**Figure 1 figure1:**
[figure not shown]
Evidence-based conceptualization illustrating how the Healthy Body and Mind Program will improve health outcomes for people with osteoarthritis and cognitive decline in community settings.

## Methods

### Ethical Considerations

All data will be deidentified and participants will be allocated a unique identification number. Personal identifying information will be stored separately from research data in a password-protected file accessible only to the research team. Deidentified research data will be stored securely for a minimum of 7 years as per institutional requirements, after which it will be destroyed. Only deidentified data will be used in publications and presentations. All participants will provide written informed consent before participation, after reading the participant information sheet and having the opportunity to ask a researcher any questions. Participation is entirely voluntary and participants may withdraw at any time without penalty or impact on their access to services. Participants who withdraw can request that their data be destroyed, provided the data has not yet been deidentified and aggregated. All participants will receive a lifestyle program provided by accredited exercise professionals and psychologists free of charge (valued at approximately US $2000). Participants who additionally take part in the focus group will receive a voucher worth US $50 to compensate for the extra time commitment involved in this component of the study. All electronic data will be stored on password-protected, encrypted devices and secure university servers. Hard copy materials will be stored in locked cabinets in a secure research office. Only named members of the research team will have access to identifiable data. Ethics approval for this study has been obtained from the UNSW Human Research Ethics Committee (HC230506). This is the third version of the protocol and aligns with approved ethics amendments (most recently approved on June 14, 2024; first approval on September 18, 2023). Changes from the first version pertained to the inclusion criteria, where “Montreal Cognitive Assessment (MoCA) [36] score 18-25 indicating mild cognitive impairment or mild dementia” was removed, and the age requirement was reduced to people aged 45 years or older. These changes were made due to recruitment challenges, although they do not change the overall aims of the study. Other amendments included changes to the terminology used in study materials (“dementia,” “cognitive decline,” and “thinking difficulties” to improve recruitment) and updates to the list of staff members. All team members received email correspondence regarding submitted changes and were requested to review amended documentation where appropriate. The clinical trial has been prospectively registered on ClinicalTrials.gov (NCT06070818). This protocol has been prepared in accordance with the SPIRIT (Standard Protocol Items: Recommendations for Intervention Trials) guidelines (Multimedia Appendix 1) [37].

### Study Design

This 12-week pilot RCT of the HBMP with a waitlist control group will use quantitative and qualitative research methodologies. Data collection will comprise the following: (1) clinical observations routinely completed as part of standard care (eg, clinical interviewing, physical assessment, and exercise monitoring), (2) validated patient-reported outcome measures (including QoL, cognition, pain, and psychological health), and (3) focus group or interviews (Table 1). Clinical observations and questionnaires will be completed at baseline (0 wk) and after intervention (12 wk). Initial community and stakeholder engagement has assisted in developing the group program and ensuring it is feasible and acceptable to participants. The study team includes accredited exercise physiologists (AEPs), accredited practicing dietitians, a health psychologist, and research assistants (RAs). All study activities will take place within the UNSW Medicine and Health Lifestyle Community Clinic facilities.

**Table 1 table1:** Data collection methods and outcome measures.

Measure or tool		Procedure (tools or guidelines)
**Clinical assessments (resting cardiovascular and anthropometry measures)**		
	Resting blood pressure and heart rate	Blood pressure will be measured using a validated automated sphygmomanometer. Participants will be seated and rested for at least 10 minutes before the blood pressure assessment [38]. Participants will place their forearm on a table with the elbow at an approximate 90° angle, and the cuff will be placed on the upper arm according to the manufacturer’s instructions. Three separate measurements will be taken on both right and left arms, with the average of the 3 measurements used in subsequent analyses.
	Waist circumference, height, weight, and BMI	Weight will be measured using a digital scale (SECA 813 model) with the participant unfasted, barefoot, and dressed in light clothing. Height will be measured barefoot using a wall-mounted stadiometer (SECA 216 stadiometer). Waist circumference will be measured according to the International Diabetes Federation guidelines [39].
	Handgrip strength	Handgrip strength will be measured using a manual dynamometer.
	Functional fitness	Functional fitness will be assessed using the submaximal 6-minute walk test [40]. The participant will be instructed to cover as much distance walking on flat ground in a laboratory setting until they have completed 6 minutes or they choose to stop walking. Risk of falls will be minimized by the AEP^a^ or RA^b^ following the participant closely to enable spotting and assistance should they lose balance. They will also monitor the participant throughout the test for safety (including heart rate and RPE^c^).
	Lower extremity function and mobility	Lower extremity function and mobility will be measured using the Short Physical Performance Battery [41], which involves timing the duration of 5 sit-to-stand repetitions from a chair, feet together, semitandem and full tandem stance, and a 2.44-m walk.
	Balance	Balance will be evaluated using the single-leg balance test. The participant will be instructed to stand on 1 foot for as long as possible without assistance up to a maximum of 60 seconds. To minimize the risk of falls, they will be supported by an AEP or RA, and there will be a wall or sturdy chair in front of them that they can hold onto if needed.
**Questionnaires**		
	APSS^d^	The APSS developed by Exercise and Sports Science Australia will be used to screen exercise readiness [42].
	Atherosclerotic Cardiovascular Disease Risk Estimator Plus	Cardiovascular disease risk will be estimated using the American College of Cardiology calculator [43].
	Active Australia Survey	Physical activity levels will be measured using the Active Australia Survey following the guide and manual for implementation, analysis, and reporting by the Australian Institute of Health and Welfare.
	Cognition (global, executive, learning, memory, and visuospatial ability)	Cognition will be assessed using the MoCA^e^ [36] and the Cambridge Neuropsychological Test Automated Battery (attention, memory, and learning tasks).
	Pain, physical health, and stiffness	Pain and stiffness will be evaluated using the WOMAC^f^ [44].
	Depression, anxiety, and stress	Psychological health will be assessed using the DASS-21^g^ [45].
	Quality of life	Quality of life will be measured using the SF-36^h^ (version 2) survey [46].

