### Objectives

We will pilot the evidence-based Healthy Body and Mind Program (HBMP), which includes PA, nutrition, lifestyle, and behavior change education on health outcomes in people living with cognitive decline and osteoarthritis. The evidence base for development of the program is outlined in Figure 1. The primary aims of this pilot randomized controlled trial (RCT) are to determine (1) the feasibility (ie, recruitment, retention, and adherence) of the HBMP for people living with osteoarthritis and cognitive decline in a community clinic and the University of New South Wales (UNSW) Medicine and Health Lifestyle Clinic, Sydney, Australia, and (2) the acceptability of the program to people living with osteoarthritis and experiencing cognitive decline. The secondary aim is to obtain pilot data on health outcomes in people with osteoarthritis and cognitive decline, following the program when compared to usual care. Health outcomes are QoL, cognition, pain, psychological health (depression, anxiety, and stress), and physical health (weight, waist circumference, blood pressure, cardiorespiratory fitness, strength, mobility, and balance). We hypothesize that individuals who complete the program will have better health outcomes when compared to the baseline and the control groups.

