### Sample Size Calculation

For pilot trials, using a 90% 1-sided CI, it is estimated that a sample size should be at least 9% of that calculated for a fully powered RCT [49]. Given a minimal clinically important difference of 0.5 SD (medium effect size), QoL measured using the Short Form Health Survey-36 [50], α of .05 (with Holm-Šídák correction), and power of 90% (β=.20) for a 2-group comparison, the required sample size would be approximately 85 participants per group (170 total). Accounting for potential dropout or attrition (15%-20%), 102 participants per group (N=204 total) would need to be recruited for a fully powered trial, and 16 participants would be required for a pilot trial. This study aims to recruit 20 participants.

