### Eligibility Criteria

Eligibility criteria will be as follows: (1) aged 45 years or older, (2) living with osteoarthritis diagnosed by a health care professional, (3) living with cognitive concerns or dementia, (4) able to safely undertake study assessments and complete exercise without assistance, and (5) have appropriate medical clearance to take part. Exclusion criteria will be as follows: (1) MoCA score of less than 18; (2) unwilling or unable to provide written informed consent and comply with study requirements; (3) inability to speak and understand English unless a translator is available; and (4) contraindications to exercise in accordance with American College of Sports Medicine (ACSM) guidelines (Multimedia Appendix 2) [51], such as symptomatic hernias, proliferative retinopathy, uncontrolled arrhythmias, or rapidly progressing or terminal illness. Consent will be obtained by the lead researcher ([name]).

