#### Health Outcomes

Baseline and postintervention assessment visits will take between 90 and 120 minutes, including the health interview, physical assessment, and questionnaire completion. The RA completing assessments will be blinded to the condition (intervention or waitlist control groups). The RA will be trained and supervised by an AEP.

Secondary outcome measures will be completed before randomization at baseline and 12 weeks after intervention. The outcome measures (questionnaires outlined in the subsequent section) will be completed by an RA and a member of the research team who is blinded to the group allocation. Health outcome measures will include QoL (measured using the Short Form Health Survey-36) [46]; cognition (MoCA [36] and the Cambridge Neuropsychological Test Automated Battery attention, learning, and memory tasks); pain (Western Ontario and McMaster Universities Osteoarthritis Index) [44,52]; psychological health (Depression, Anxiety, and Stress Scale-21) [45]); and physical health (weight, waist circumference, blood pressure, functional fitness, strength, mobility, and balance). Balance exercises will be simple easy to perform movements that take place in a purposefully designed environment that minimizes the risk of falls (ie, they will be beside a wall, with an AEP closely monitoring them and simple exercises will be completed first, enabling the AEP to continually assess whether it is safe for the participant to continue to the slightly more challenging balance exercises).

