The questionnaires (Table 1) will assess the participants’ health relevant to the outcome measures (eg, cognition, QoL, and psychological health). The data collection process will be administered using UNSW Qualtrics, except for the cognition measures, as these require the participant to draw on the printed tool (ie, pen and paper questionnaire). Participants will be asked questions by an experienced health psychologist and RA who has experience interviewing people with cognitive decline. They will enter the data directly onto a tablet or paper for the MoCA (with no identifying information, just a participant ID). The MoCA data will then be entered electronically. The health psychologist has received appropriate training to administer the MoCA [36] and a license (obtained in July 2022) and permission to train other staff and students to administer the tool. Participants will be invited to bring a support person with them if they wish, given that variability in level of independence is expected in this population (people with osteoarthritis and cognitive decline). All questionnaires have been validated and used extensively in the literature and with clinical populations, including people with osteoarthritis and cognitive decline.

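### Entry admits osteoarthritis of any joint, but pain is assigned only to the hip-and-knee WOMAC and pooled over everyone, so the pilot's pain estimate may be diluted and will be hard to interpret

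*Protocol article*

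**What the plan says.** All references are to the protocol article.

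- **Entry.** Eligibility Criteria asks for people "living with osteoarthritis diagnosed by a health care professional". No joint is named, and none of the exclusions removes hand, shoulder or spine disease.
- **Pain instrument.** Table 1, under Questionnaires, states "Pain and stiffness will be evaluated using the WOMAC". The Health Outcomes section repeats the choice: "pain (Western Ontario and McMaster Universities Osteoarthritis Index". No other tool is assigned to pain, and neither place ties WOMAC to an index joint.
- **Other patient-reported data.** Table 1 also lists version 2 of the SF-36, for a different purpose: "Quality of life will be measured using the SF-36".
- **Validation.** Health Outcomes gives a general assurance: "All questionnaires have been validated and used extensively in the literature and with clinical populations, including people with osteoarthritis and cognitive decline". It does not mention joint site.
- **Analysis.** Statistical Analysis and Clinical Interpretation compares health outcomes before and after the program and between arms, by t tests and repeated measures ANOVA, with no split by affected joint.
- **Status of pain.** Pain is one of several outcomes under the secondary aim in Objectives: "The secondary aim is to obtain pilot data on health outcomes in people with osteoarthritis and cognitive decline". Anticipated Findings includes pain among the outcomes expected to improve.

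**The concern.** The population is defined by osteoarthritis at any site, and the pain measure is specific to two sites. A participant admitted for hand osteoarthritis, with sound hips and knees, could have considerable pain that WOMAC hardly registers. Such a participant would contribute little change to the arm mean whatever the program did for the pain.

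Nothing else in the article narrows the population to hip or knee disease. The resistance exercises in Table 2 include upper-body work (seated row, chest press, lat pull-down), so the program itself does not imply a lower-limb sample.

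What is at stake is the pain estimate that the pilot hands on. The abstract says that the findings are to inform larger trials. A WOMAC mean change and SD from an unstated mix of joints describes neither a hip-and-knee population nor an all-joint one, and a reader could not tell which it is closer to.

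**Working it through.** **1. Alignment of population and measure.** Setting the sections side by side: Eligibility Criteria has no joint restriction; Table 1 and Health Outcomes assign WOMAC alone to pain; the analysis section has no split by joint. Recruitment says that chronic disease history is documented, but not that the affected joint is recorded. The mismatch therefore rests on stated design choices plus one property of the named instrument, its hip and knee scope.

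**2. The plan's own figure.** Sample Size Calculation is built on quality of life: "Given a minimal clinically important difference of 0.5 SD (medium effect size), QoL measured using the Short Form Health Survey-36", with "α of .05 (with Holm-Šídák correction" and 90% power (beta is printed as .20, which does not agree with 90%). The formula is

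n per group = 2 × (z₁₋α/₂ + z₁₋β)² / d²

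With two-sided α = 0.05, 90% power and d = 0.5: 2 × (1.960 + 1.282)² / 0.25 ≈ 84.1, rounded up to **85**, as stated. Neither 80% power two-sided (63) nor 90% power one-sided (69) gives 85. The calculation concerns the SF-36, so the WOMAC point changes no stated figure.

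**3. Size of a possible dilution.** The inputs here are assumptions. Let f be the share of participants whose osteoarthritis WOMAC does not register, with exactly zero change in them and the SD held fixed. The true pain effect is taken as 0.5 SD, borrowed from the quality-of-life calculation because the article gives no figure for WOMAC. Then

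observed effect = 0.5 × (1 − f)

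The third column applies the formula in step 2 (two-sided 5%, 90% power) to a later trial sized on pain. The last is normal-approximation power of a one-sided 5% test at the planned 10 per arm.

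| f (assumed) | Effect (SD) | n per group, later trial | Pilot power, 10 per arm |
|---|---|---|---|
| 0 | 0.50 | 85 | 30% |
| 0.1 | 0.45 | 104 | 26% |
| 0.2 | 0.40 | 132 | 23% |
| 0.3 | 0.35 | 172 | 19% |
| 0.4 | 0.30 | 234 | 17% |
| 0.5 | 0.25 | 337 | 14% |

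The first row shows that the pilot is uninformative about efficacy on pain even without dilution. The third column shows where the problem would be felt: in a later trial planned on this estimate.

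**The case against.** **The documents do not describe the instruments.** Neither WOMAC's items nor the SF-36 subscales appear in the article, and the article does vouch for all its questionnaires in osteoarthritis. The first part is true, so the point depends on the content of two named instruments. That content can be checked on the forms the trial uses; it is not a recalled study result. The general assurance does not settle the matter, because it does not speak to joint site.

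**The mechanism can be overstated.** A reader might infer that participants without hip or knee osteoarthritis cannot improve on WOMAC, or that any effect is bound to be diluted. The documents do not support that. The joint mix is not given, and everyone enrolled may have hip or knee disease. A person who qualified on another joint may also have hip or knee pain. This objection stands, and the arithmetic above shows only what follows from an assumed share.

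**The consequence is limited.** Pain is a secondary outcome of a 20-person pilot, and the parenthetical list of preliminary-efficacy outcomes in the analysis section omits it. Anticipated Findings already warns that improvements may not reach significance. This stands too. It limits the importance of the point but does not make the pooled estimate easier to read.

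**The remedy could do harm.** A reader might conclude that SF-36 bodily pain should replace WOMAC as the pain outcome. Results reports 18 participants enrolled with their data collected, so a replacement now would be a change of outcome after the data are in. This objection stands against replacement, but not against a disclosed supplementary result.

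**An article condenses.** Index-joint instructions or subscale reporting may exist in a fuller document. That is possible, and their absence is not the point here. The point is that the stated entry criterion, pain measure and pooled comparison do not fit together for osteoarthritis outside the hip and knee.

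**Conclusion.** The concern holds in a conditional form. Entry is open to any joint, the only designated measure of pain and stiffness is built around the hip and knee, and everyone is pooled. If some participants have osteoarthritis only elsewhere, the pooled WOMAC change may be diluted. Until the joint mix is reported, the estimate is hard to interpret or carry forward.

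Its size cannot be derived from the documents. Under the assumptions in the working (zero WOMAC change in the affected share, fixed SD, a true effect of 0.5 SD), shares of 10% to 50% would reduce the effect to 0.45 to 0.25 SD, and a later trial sized on pain would need 104 to 337 per group instead of 85. With a share of zero there is no dilution.

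The primary aims (feasibility and acceptability) and the stated 85 per group are not affected. Nor do the documents support saying that the pain result will be wrong. This is a modest point worth acting on because the remedy is cheap.

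**What to change.** 1. Keep WOMAC as specified, for all randomised participants.
2. In Health Outcomes and in Statistical Analysis and Clinical Interpretation, add the SF-36 version 2 bodily-pain score as a supplementary, joint-independent pain outcome in all participants. State plainly that it was added after data collection.
3. Where existing records identify the affected joint, report the number with hip or knee osteoarthritis in each arm and the WOMAC results in that subgroup. Where they do not, say so.

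**Cost.** No new instrument or visit is needed, because the SF-36 is already collected. The price is one extra secondary analysis and a check of records that may not name the joint. The WOMAC subgroup will be small and imprecise, and should be presented descriptively. The bodily-pain score is not specific to osteoarthritis and does not cover stiffness, which is a further reason to retain WOMAC.

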**Qualitative methods**		
	Participant feedback and recommendations	Participant feedback and recommendations will be obtained through focus groups or interviews using semistructured questions [47].
	Individual or stakeholder feedback and recommendations	Individual and stakeholder perspectives will be gathered through stakeholder meetings or workshops using a semistructured format.
Adverse events		Adverse events will be monitored and reported in accordance with CONSORT^i^ guidelines [48].

^a^AEP: accredited exercise physiologist.

^b^RA: research assistant.

^c^RPE: rating of perceived exertion.

^d^APSS: Adult Pre-Exercise Screening System.

^e^MoCA: Montreal Cognitive Assessment.

^f^WOMAC: Western Ontario and McMaster Universities Osteoarthritis Index.

^g^DASS-21: Depression, Anxiety, and Stress Scale-21.

^h^SF-36: Short Form Health Survey-36.

^i^CONSORT: Consolidated Standards of Reporting Trials.

### Sample Size Calculation

For pilot trials, using a 90% 1-sided CI, it is estimated that a sample size should be at least 9% of that calculated for a fully powered RCT [49]. Given a minimal clinically important difference of 0.5 SD (medium effect size), QoL measured using the Short Form Health Survey-36 [50], α of .05 (with Holm-Šídák correction), and power of 90% (β=.20) for a 2-group comparison, the required sample size would be approximately 85 participants per group (170 total). Accounting for potential dropout or attrition (15%-20%), 102 participants per group (N=204 total) would need to be recruited for a fully powered trial, and 16 participants would be required for a pilot trial. This study aims to recruit 20 participants.

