Following successful screening, the participant will be allocated a unique ID number using the generated list. The RA who performs the randomization will advise the data collectors of the participants’ IDs by referring to the password-protected spreadsheet of participant names and allocated ID numbers. After completion of baseline testing, participants will be randomly assigned to the intervention (n=10) or waitlist control groups (n=10) using a computer-generated randomization list produced by a researcher external to the study group. In total, 20 participants will complete the program. After completing a 12-week period of usual care, those in the waitlist control group will then complete the 12-week HBMP. A 12-week follow-up will be performed to examine sustainability. Participants are allowed to withdraw from the trial at any time they wish and are assured that doing so would not alter their care or relationship with the university or the community clinic.

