## Results

As of October 2025, we have enrolled 18 participants and completed their data collection. Results are expected to be published during the first quarter of 2026.

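### The pilot's 9% fraction does not correspond to the 90% one-sided confidence interval that it is tied to; the design supports about 83% to 86%

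*Protocol article*

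**What the plan says.** All of this stands in one paragraph of the protocol article, under Sample Size Calculation.

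- Pilot rule, attributed to a cited source: "using a 90% 1-sided CI, it is estimated that a sample size should be at least 9% of that calculated for a fully powered RCT".
- Full-trial effect: "Given a minimal clinically important difference of 0.5 SD (medium effect size", on the SF-36.
- Error rates: "α of .05 (with Holm-Šídák correction" and "power of 90% (β=.20) for a 2-group comparison".
- Result for the full trial: "the required sample size would be approximately 85 participants per group (170 total".
- After an allowance of 15% to 20% for attrition: "N=204 total) would need to be recruited for a fully powered trial, and 16 participants would be required for a pilot trial".
- The recruitment target is 20. The Recruitment section splits it 10 and 10, and the Results section reports 18 enrolled.

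**The concern.** A pilot sized as a fraction of the main trial takes that fraction from two things: the confidence level of the pilot's interval, and the error rates of the main trial. The paragraph gives all of these, so the 9% can be checked, and at a 90% one-sided level it looks too small by roughly half.

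What is at stake is the description of the pilot's precision. The 90% level is the only statistical justification offered for the pilot's size, and the findings are meant to inform larger trials. Readers planning such a trial, or copying the rule, would credit a pilot of 16 to 20 with more confidence than it has. The check is also hampered because 90% power and β=.20 describe different trials and lead to different fractions.

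**Working it through.** **Inputs.** From Sample Size Calculation: difference δ = 0.5 SD, α = .05, power 90% or 80% (both are implied), 170 calculated, 9%, pilot 16, target 20. From Recruitment: equal arms. From Results: 18 enrolled. α is taken as two-sided, because one-sided α gives only 69 per group at 90% power and 50 at 80%.

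**1. Reproduce the full-trial figure.** n per group = 2(z₁₋α/₂ + z_power)²/δ².

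- 90% power: 2 × (1.960 + 1.282)²/0.25 = 2 × 10.507/0.25 = 84.06, so 85.
- 80% power: 2 × (1.960 + 0.842)²/0.25 = 2 × 7.849/0.25 = 62.8, so 63.

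At the unadjusted 5% level, 85 is therefore the 90%-power figure (β=.10). One other route comes close. A Šídák step for three comparisons (α = 1 − .95^(1/3) = .01695) at 80% power gives 84 by this formula, and 84.9, so 85, by the t-based calculation. The paragraph does not state a number of comparisons, so this route is carried below only as a sensitivity check.

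**2. Reproduce the pilot figure.** 0.09 × 170 = 15.3, so 16. Allowing for 20% loss, 16/0.80 = 20, the stated target.

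**3. Which fraction goes with which confidence level?** Assumed rule: with an observed difference of zero, the one-sided limit at level c falls at δ. With m per arm, z_c × √(2/m) = δ, so m = 2z_c²/δ². Dividing by n from step 1:

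fraction = z_c² / (z₁₋α/₂ + z_power)².

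| One-sided level | 90% power | 80% power | 80% power, three-comparison α |
|---|---|---|---|
| 90% | 1.642/10.507 = 15.6% | 1.642/7.849 = 20.9% | 15.7% |
| 80% | 0.708/10.507 = 6.7% | 0.708/7.849 = 9.0% | 6.8% |

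With one-sided α, the 90% row becomes 19.2% (90% power) and 26.6% (80% power). No cell in the 90% row is near 9%. The only match is an 80% interval at 80% power.

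In participants, 15.6% of 170 is 26.6, so 27, or 28 with equal arms. Applying 20.9% to the total that 80% power needs (2 × 63 = 126) gives 26.4, the same answer. Applied to 170 it would be 35.6, so 36.

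**4. Which level does 9% imply?** Level = Φ(√0.09 × (z₁₋α/₂ + z_power)).

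- 90% power: Φ(0.3 × 3.242) = Φ(0.972) = 0.8346, about 83%.
- 80% power: Φ(0.3 × 2.802) = Φ(0.840) = 0.7997, about 80%.

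**5. Direct check without the ratio.** With m per arm, the 90% half-width in SD units is t(.90; 2m − 2) × √(2/m). The confidence with which 0.5 SD is excluded at a zero difference is the t probability below 0.5/√(2/m).

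| Total | √(2/m) | 90% half-width | Confidence at 0.5 SD |
|---|---|---|---|
| 16 | 0.500 | 0.673 SD | 83.3% |
| 18 | 0.471 | 0.630 SD | 84.8% |
| 20 | 0.447 | 0.595 SD | 86.1% |
| 28 | 0.378 | 0.497 SD | 90.1% |

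Normal quantiles give 84.1%, 85.6% and 86.8% for the first three rows. The 80% half-width with 16 is 0.434 SD, so a claim of at least 80% is true at every size considered.

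**The case against.** The strongest reply is that the paragraph gives no formula. It takes the 90% and 9% pairing from a cited source that is not at hand, so the ratio in step 3 is an assumption. That stands as a condition. Two things support the assumption: it returns 9.0% exactly for one conventional pair of settings, and step 5 needs only the 0.5 SD and equal arms. Step 5 does still assume that the interval is meant to exclude 0.5 SD, which the paragraph does not say outright.

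The second reply is that little depends on it, and this is largely right. The primary aims are feasibility and acceptability. The Statistical Analysis section plans t tests and ANOVAs, with no 90% limit set against the MCID and no progression rule. The Discussion warns that improvements may not reach significance. A reader might infer that a null pilot would be taken as ruling out 0.5 SD with 90% confidence, but nothing in the plan uses the result that way.

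Three further inferences are tempting and are not supported:

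- **That 16 is an arithmetic error against 204.** The two figures share a sentence, and 9% of 204 is 18.36, so 19. But the rule refers to the number calculated for the full trial. That is 170; 204 is the number to recruit. The target of 20 exceeds 19 in any case.
- **That only 14 to 15 will be evaluable.** Applying 15% to 20% loss to 18 gives 15.3 to 14.4. But the Results section says "we have enrolled 18 participants and completed their data collection", so attrition is no longer a projection.
- **That "In total, 20 participants will complete the program" denies any attrition.** It stands between the 10/10 allocation and the waitlist arm's later program, and reads naturally as saying that both arms receive it.

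**Conclusion.** The point holds as a mislabelled confidence level in the sample size justification. Under the assumed rule, a 90% one-sided interval needs 15.6% of the full trial at 90% power or 20.9% at 80% power, against the 9% stated. For 0.5 SD that is about 27 to 28 participants rather than 16. The design supports about 83% one-sided confidence at 16, 85% at 18 and 86% at 20. These levels assume two equal arms, all participants evaluable, and an interval meant to exclude the MCID at a zero observed difference.

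The 9% itself was applied correctly to 170, and the target of 20 is consistent with it. Neither enrolment nor the planned analysis is affected. The conflict between 90% power and β=.20 belongs to the same correction: 9% corresponds to about 83% under the first and 80% under the second. At the unadjusted 5% level, only the first yields 85 per group.

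**What to change.** Revise the paragraph in three places.

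1. Replace the 90% one-sided level with the one actually supported: at least 80%, being about 83% at 16 and about 85% with the 18 enrolled. State the rule used, namely that the limit excludes 0.5 SD at a zero observed difference. Writing 80% as the level that yields 9% would not fully cohere, because at 90% power an 80% interval gives 6.7%; reporting the achieved level avoids this.
2. Reconcile the power with β. If 85 per group was calculated at an unadjusted two-sided .05, the matching pair is 90% power and β=.10. If it came from 80% power with a Holm-Šídák adjustment, give the number of comparisons.
3. For clarity only, say that 16 is 9% of the 170 calculated and that 20 allows for 20% loss (16/0.80).

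The cost is a few words and a less favourable confidence figure. No participants are added and no analysis changes.
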